#### 2.8.3 Chronic Fatigue Syndrome

Symptoms of chronic fatigue syndrome (CFS) (93) that affects more than 50% of breast cancer patients and the extent of psychological stress will be assessed using the Distress Thermometer (DT) (96).

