**Methods:**

The prospective observational BEGYN study will include 110 non-metastatic breast cancer patients. The patients will be assessed during a base line visit prior to the initiation of the antineoplastic therapy and after 3, 6, 9 and 12 months. The physical activity will be measured using a fitness tracker and a self-assessment diary during the entire study. Each visit will include the assessment of (i) cardiorespiratory fitness measured by spiroergometry, (ii) body composition, (iii) psycho-emotional parameters (quality of life, mental health, fatigue, depression, distress, anxiety, well-being), and (iv) extensive blood tests including routine laboratory, vitamin D, selenium and immunologically relevant biomarkers (e.g., leukocyte subpopulations and cytokine profiles).

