### 2.8 Assessment of Psychological Parameters

The assessment of psychological parameters will be performed by using standardized questionnaires that were validated for (breast) cancer patients, respectively (89–98). A list of questionnaires is shown in **Table 8**. Moreover, the patients have the opportunity to report individual thoughts as free texts and during the study visits.

**Table 8 T8:** Assessment of the psychological parameters (used questionnaires).

Abbreviation	Name	Nmber of items	Content	Reference
**EORTC QLQ-C30**	European Organization for Research and Treatment of Cancer Quality of Life Questionnaire-Core 30	30 items	health-related quality of life (QoL)	(95)
**EORTC QLQ-BR23**	European Organization for Research and Treatment of Cancer Quality of Life Questionnaire-BReast cancer module 23	23 items	health-related quality of life (QoL) in breast cancer patients: systemic therapy side-effects, arm symptoms, breast symptoms, body image and sexual functioning	(95)
**MHS**	Mental Health Scales	76 items	willpower, acceptance of life, self-reflection, finding of a meaning, naturalness and social integration	(92)
**HADS**	Hospital Anxiety and Depression Scale	14 items	level of anxiety and level of depression	(89)
**DT**	Distress Thermometer	DT: 1 item	Psychosocial distress and possibly associated problems (practical, family, emotional, spiritual/religious and physical)	(94)
		Problem list: 39 items		
**MDWQ**	MultiDimensional Well-being Questionnaire	12 items	mood, level of alertness and level of calmness	(91)

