#### 2.8.4 Anxiety and Depression

The self reported anxiety and distress will be assessed using the HADS (Hospital Anxiety and Depression Scale) questionnaire (89, 97) and the German adaptation of the Distress Thermometer (DT) (94, 96–98).

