#### 2.8.5 Well-Being

To get an overview of the mental state of the patients, the German questionnaire “Multidimensional Well-being Questionnaire” (MDBQ) (91) has been used in its short version with twelve items (short version A). This questionnaire captures three bipolar dimensions of the current mental state (good mood – bad mood, alertness – fatigue, tranquility – inquietude) of the breast cancer patients. The questionnaire presents twelve adjectives (e.g., satisfied, flabby, good etc.) and with the help of a five-point Likert-scale (*1* = *not at all*; *5* = *very much*) the patients rate their instant feeling. Cronbachs’α is between 0.86 and 0.94, indicating a good consistency of the scale.

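### Section 2.8.3 assigns fatigue to the Distress Thermometer, so a fatigue result may be indistinguishable from distress or rest on a single problem-list item

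*Protocol article*

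**What the plan says.** The Abstract (Methods) states that every visit assesses "psycho-emotional parameters (quality of life, mental health, fatigue, depression, distress, anxiety, well-being". Fatigue and distress are two separate entries in that list.

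Section 2.8.3 is the only section headed fatigue. Its single sentence has two subjects, chronic fatigue syndrome symptoms and psychological stress, and gives both one instrument: "that affects more than 50% of breast cancer patients and the extent of psychological stress will be assessed using the Distress Thermometer (DT".

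Table 8 (section 2.8) gives the content of the Distress Thermometer (DT) as "Psychosocial distress and possibly associated problems (practical, family, emotional, spiritual/religious and physical". The thermometer itself has one item, and a second line adds "Problem list: 39 items". No row of Table 8 names fatigue as content.

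Section 2.8.4 uses the DT a second time, next to another scale: "The self reported anxiety and distress will be assessed using the HADS (Hospital Anxiety and Depression Scale) questionnaire" and the German adaptation of the DT.

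Section 2.8.5 describes a 12-item well-being questionnaire (MDBQ in the text, MDWQ in Table 8) that covers "three bipolar dimensions of the current mental state (good mood – bad mood, alertness – fatigue, tranquility – inquietude". It adds that "the patients rate their instant feeling". The article files this questionnaire under well-being and does not link it to the fatigue outcome.

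**The concern.** Fatigue is one of the reasons given for the study. Section 1 cites exercise in the management of cancer-related fatigue, and section 3.1 singles fatigue out as an area where activity appears to help. A reader will therefore expect an activity-fatigue result.

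Under section 2.8.3 that result would come from an instrument that the article's own table describes as a measure of distress, and which also supplies a distress result. The same number could then be reported under two names, or fatigue could be reduced to one entry on a list of problems. This is a stated assignment of instrument to outcome, so it is more than a detail left to a fuller document.

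The construct label is also unsettled. Section 2.8.3 speaks of chronic fatigue syndrome and section 1 of cancer-related fatigue syndrome.

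**Working it through.** **1. The plan's own figures.** Section 2.9 gives precision for 110 patients.
- Mean, SD 15.0: t(0.975; 109) × 15/√110 = 2.8346, stated as 2.835.
- Proportion 0.50: 2 × 1.96 × √(0.25/110) = 0.1869, stated as 0.187.

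Both reproduce. Neither involves a fatigue measure, so the point does not touch the sample size statement.

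**2. The passages side by side.**

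| Place | Fatigue | Distress |
|---|---|---|
| Abstract, Methods | listed | listed separately |
| Section 2.8.3 | DT | DT (as psychological stress) |
| Section 2.8.4 | not mentioned | HADS and DT |
| Table 8, DT row | not named | named as content |
| Section 2.8.5 | one of three dimensions | not mentioned |

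The DT can yield a fatigue variable in two ways.
- *Thermometer score.* Fatigue and DT distress are then the same variable.
- *Problem-list item.* Table 8 includes physical problems, so a fatigue item is possible. The article neither names one nor says how it would be scored.

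**3. Can a size be given? Thermometer score.** Let r be the true activity-fatigue correlation (absolute size), v the correlation of the thermometer with fatigue, and q the correlation of activity with the part of distress unrelated to fatigue. The document gives none of them. The observed correlation is

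v·r + √(1 − v²)·q.

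Assume r = 0.30 and v = 0.4 to 0.6.
- With q = 0: 0.4 × 0.30 = 0.12 and 0.6 × 0.30 = 0.18. Power at n = 110, two-sided 0.05, from atanh(observed) × √107 − 1.96, is 24% and 47%, against 89% for an undiluted 0.30.
- With q = 0.15 and v = 0.6: 0.18 + 0.8 × 0.15 = 0.30, so there is no dilution. A larger q gives inflation.
- For v = 0.4 the break-even is q = 0.30 × √(0.6/1.4) = 0.196.

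Section 1 states that physical activity can affect anxiety and depression, so q = 0 cannot be taken for granted. The direction is open.

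**4. Can a size be given? Problem-list item.** If the item is yes/no (Table 8 does not say) and stands for an error-free normal score, the information kept is φ(z)²/[p(1 − p)].
- p = 0.5: 0.637, and 0.637 × 110 = 70 patients.
- p = 0.3: 0.3477²/0.21 = 0.576, and 0.576 × 110 = 63 patients.

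The 50% echoes section 2.8.3. The 30% in section 1 refers to disease-free survivors, not to patients in their first year of treatment. No collected score is shown to be the error-free comparator. These figures show only that such an item is coarse.

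**The case against.** The strongest reply has four parts.

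- *The DT is more than one item.* Table 8 adds a 39-item list with physical problems, and section 2.8.3 speaks of symptoms, which fits use of that list. Item-level scoring is commonly left to a fuller document. This stands: a reader might infer that fatigue rests on a one-item distress scale, and the documents do not support that. It does not remove the problem, because a single list item remains a weak basis for a named outcome.
- *Distress has a second measure.* Section 2.8.4 also uses the HADS. This stands too: the claim that fatigue and distress can never be told apart would go too far. It holds only if the thermometer score is used for both.
- *No better measure is proven.* The dimension "good mood – bad mood, alertness – fatigue, tranquility – inquietude" rates the instant feeling. The Cronbach's alpha of 0.86 to 0.94 concerns consistency, not validity for a fatigue syndrome. The article describes the QLQ-C30 only as a quality-of-life questionnaire with a 0 to 100 score and mentions no fatigue scale. This limits how firmly a replacement can be named.
- *The stakes are limited.* Section 2.9 calls the analyses explorative, fatigue is one of seven listed parameters, and all questionnaires are collected anyway. This stands, and it bears on severity only.

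A reader might also infer that activity-fatigue associations will be diluted. Without a known relation between the DT and fatigue, and with activity possibly related to distress itself, the documents do not support that.

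**Conclusion.** The point holds as an assignment problem. Section 2.8.3 gives fatigue to an instrument that Table 8 describes as distress plus a problem list, while the Abstract treats fatigue and distress as separate. The consequence depends on which part of the DT is used: a result that cannot be separated from distress, or a coarse indicator.

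No size or direction of bias follows from the document. The figures above rest on assumed correlations and on an assumed yes/no item, and serve as illustration only.

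The 30% and the more than 50% quoted for fatigue refer to different populations, so they are not in conflict. Only the two names for the construct need reconciling.

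This should be corrected before analysis. It does not threaten the study as a whole.

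**What to change.** - Use the DT for distress only.
- Before analysis, define the fatigue outcome by a multi-item score from questionnaires already administered. The MDBQ alertness-fatigue dimension is the one the article itself shows; state that it rates the momentary state. Add a QLQ-C30 fatigue symptom score once its existence and scoring have been confirmed in the questionnaire's manual, and say which of the two leads.
- Treat any fatigue item on the problem list as supportive, and name the item and its scoring.
- Use one term for the construct in sections 1 and 2.8.3.

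The cost is a change of wording and a scoring rule. Section 3.3 says recruitment ended in January 2021 and data collection runs to March 2022, so no instrument could be added at baseline, and none is needed. Because section 2.9 plans no correction for multiple testing, fixing the score in advance also prevents a choice among several fatigue variables after the results are seen.

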#### 2.8.4 Anxiety and Depression

The self reported anxiety and distress will be assessed using the HADS (Hospital Anxiety and Depression Scale) questionnaire (89, 97) and the German adaptation of the Distress Thermometer (DT) (94, 96–98).

#### 2.8.5 Well-Being

To get an overview of the mental state of the patients, the German questionnaire “Multidimensional Well-being Questionnaire” (MDBQ) (91) has been used in its short version with twelve items (short version A). This questionnaire captures three bipolar dimensions of the current mental state (good mood – bad mood, alertness – fatigue, tranquility – inquietude) of the breast cancer patients. The questionnaire presents twelve adjectives (e.g., satisfied, flabby, good etc.) and with the help of a five-point Likert-scale (*1* = *not at all*; *5* = *very much*) the patients rate their instant feeling. Cronbachs’α is between 0.86 and 0.94, indicating a good consistency of the scale.

### 2.9 Sample Size Calculation and Statistical Analyses

The Institute for Medical Biometry, Epidemiology and Medical Informatics (IMBEI) Saarland University is supporting the sample size calculation, study design, data management and evaluation using PASS 2019 (NCSS, LLC, Kaysville, Utah, USA) and SPSS (Version 27 IBM SPSS Statistics, Armonk, New York, USA). Data were collected by using Excel 2019 (Microsoft, Redmond, USA). A sample size of 110 produces a two-sided 95% confidence interval with a distance from the mean to the limits that is equal to 2.835 when the estimated standard deviation is 15.0. A sample size of 110 produces a two-sided 95% confidence interval with a width equal to 0.187 when the sample proportion is 0.50.

Continuous measures are presented as means ± standard deviations (SD) or medians (range). Categorical variables are presented as frequencies (percentage). For continuous variables normality is tested using Shapiro-Wilk-Test. In case of non-rejection of normality two-group comparisons are due to the t-test for two independent samples. For more than two groups, comparisons are due to one-way Analysis of Variance (ANOVA). Comparing two repeated measurements, t-test for 2 dependent samples is used and for more than two we use repeated measures ANOVA. In case of rejection of normality, Mann-Whitney U-test, Kruskal-Wallis-test, Wilcoxon test for two dependent samples and Friedman-test are used, respectively. For group comparisons considering categorical variables the chi-squared test and for repeated measures McNemars’s test are applied. Considering possible confounding we use subgroup analyses for categorical subgroups or propensity-score-matching otherwise. Statistical significance will be calculated using appropriate statistical methods with two-sided p-values < 0.05. The statistical analyses are explorative, so there will be no correction for multiple testing.

Data cleanup will include tests for missing data and plausibility. Depending on the degree of incompleteness or lack of accuracy, all, or some of the data from a patient will be excluded from further evaluation. In the case of a study drop out prior the last follow up visit, the patient’s data will only be included, and tests will be performed to identify potential predictors for a study drop-out (e.g., age or weight) that might introduce a bias. The risk of bias will be discussed in any publications of the data.

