#### 3.1.3 Comparison of Different Antineoplastic Therapies

The BEGYN study will allow to compare patients with various antineoplastic therapies, i.e., endocrine therapy, chemotherapy, surgery, and radiotherapy. Due to the strict adherence to the national guideline, therapy concepts are to be expected representative for the German national standard.

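### Subgroup analysis and propensity-score matching, the only confounder controls named, do not fit a continuous activity exposure that changes over 12 months; adjusted longitudinal regression on all 110 patients would.

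*Protocol article*

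**What the plan says.** On confounding, section 2.9 of the protocol article has one sentence: "Considering possible confounding we use subgroup analyses for categorical subgroups or propensity-score-matching otherwise". The other methods listed there are tests between groups or between repeated measurements: t-tests, ANOVA, their rank-based counterparts, chi-squared and McNemar. No regression, covariance analysis, mixed model or correlation is named. Significance is covered in general terms: "Statistical significance will be calculated using appropriate statistical methods with two-sided p-values < 0.05". The analyses are labelled explorative.

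The design these methods must serve is a single cohort: "The prospective observational BEGYN study will include 110 non-metastatic breast cancer patients". The abstract gives the aim as relating the extent of physical activity to fitness, body composition, biomarkers and psycho-emotional measures. Section 2.4.1 expresses activity as MET, and section 2.4.3 adds daily tracker values such as steps. Section 2.2 puts the baseline visit before any antineoplastic therapy, with quarterly visits afterwards. Section 3.1.3 also expects to "compare patients with various antineoplastic therapies, i.e., endocrine therapy, chemotherapy, surgery, and radiotherapy", with the remark "Due to the strict adherence to the national guideline".

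**The concern.** Conventional propensity-score matching pairs an exposed patient with an unexposed one. Activity here is a quantity that varies between patients and within each patient over the year, and the article defines no activity groups. To match at all, the analyst must choose a cut-point, probably after seeing the data. The choice discards the dose information that a year of tracker and diary data was meant to supply, and patients without a match leave the analysis.

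Therapy raises a second difficulty. Section 2.7.2 says that both antineoplastic therapy and physical activity can strongly affect the immune system, so therapy is an obvious candidate confounder. It begins after baseline and may differ at months 3, 6, 9 and 12. A propensity score built from baseline data cannot contain it.

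Subgroup analysis can hold one categorical factor fixed, and more by cross-classification, but the cells soon become too small. At stake are the credibility and precision of the activity associations, which are the study's main product.

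**Working it through.** **1. The plan's own figures.** For a mean, assuming an SD of 15, section 2.9 gives a "two-sided 95% confidence interval with a distance from the mean to the limits that is equal to 2.835". For a proportion, the figure given is a "confidence interval with a width equal to 0.187 when the sample proportion is 0.50".
- Mean: t(0.975, 109) × 15 / √110 = 2.835. Reproduced.
- Proportion: 2 × 1.96 × √(0.25/110) = 0.187. Reproduced.

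Both describe one estimate in all 110 patients. Neither describes a contrast between activity levels.

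**2. Two-group difference, SD 15.** Half-width = t(0.975, n1+n2−2) × 15 × √(1/n1 + 1/n2).
- 55 v 55, unadjusted: 5.67
- 35 v 35: 7.16
- 30 v 30: 7.75

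The 30 to 35 pairs (55 to 64% of patients) are an assumption, and the pairs are analysed as independent groups.

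**3. Fair comparator.** An adjusted analysis of all 110 also pays for confounding. Its variance is inflated by 1/(1−R²), where R² is the share of exposure variance explained by the covariates. Assuming R² of 0.2 to 0.3:
- 5.67 / √0.8 = 6.34
- 5.67 / √0.7 = 6.78

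This ignores any gain from covariates that predict the outcome. Ratios of matched to adjusted half-width:

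| | R² = 0.2 (6.34) | R² = 0.3 (6.78) |
|---|---|---|
| 35 pairs (7.16) | 1.13 | 1.06 |
| 30 pairs (7.75) | 1.22 | 1.14 |

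The range is 6 to 22%. Stronger confounding also leaves fewer matches, so the two extremes combine assumptions that fit together less well than the 13 to 14% on the diagonal.

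**4. Simulation of patients lost and of the cost of cutting.** All inputs are assumed: n = 110, five confounders, a linear effect of 0.25 per SD of activity, 1:1 nearest-neighbour matching without replacement, a caliper of 0.2 SD of the logit, and 600 replicates per scenario. Activity was cut at the median.

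| R² of activity on confounders | Patients kept by matching | Power: continuous, adjusted | Power: cut, adjusted, all 110 | Power: cut and matched |
|---|---|---|---|---|
| 0.1 | 75 | 76% | 50% | 38% |
| 0.2 | 69 | 70% | 47% | 35% |
| 0.3 | 63 | 61% | 38% | 29% |
| 0.5 | 52 | 43% | 22% | 19% |

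Matching drops 31 to 53% of patients here. With the upper third set against the rest it keeps 62, 58, 54 and 45, a loss of 43 to 59%, part of which 1:1 matching imposes by design. Going from the third column to the fourth isolates the cut; going from the fourth to the fifth isolates matching. The cut costs more. The simulated effect is linear, which favours the continuous model.

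**5. Subgroups.** At SD 15 the half-width of a mean is 4.06 with n = 55 and 5.93 with n = 27, against 2.835 in all 110. Three binary confounders give 8 cells averaging 110/8 ≈ 14 patients; four give 16 cells averaging about 7.

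**The case against.** The best defence is that the analyses are explorative, that the limitations at the end of section 3.1 ask for care over causality, and that a journal article leaves detail to a fuller plan. Generalised and time-dependent propensity methods exist, and the general reference to appropriate methods might be read as leaving room for regression. Some of this stands: the consequence is softened, and the form of matching could be specified elsewhere. But the article does choose a confounding method. It names matching beside group-comparison tests, and the explorative label is used there to justify not correcting for multiple testing. It does not make the method fit the aim.

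Three stronger readings are tempting, and the document does not support them.
- A reader might infer that independent-sample tests fail because one patient can receive several of the listed therapies. Section 3.1.3 specifies no four-arm test, and chemotherapy yes against no gives disjoint groups. Overlap, itself inferred, creates confounding by co-treatment; it does not break independence.
- A reader might infer that guideline-driven treatment pushes propensity scores to near 0 or 1. The guideline remark supports representativeness only. Limited overlap is plausible but unmeasured. It would concern therapy contrasts, not activity, and regression would not cure it.
- A reader might conclude that intervals become 26 to 43% wider. That sets 7.16 (35 pairs) and 8.11 (27 v 28, one half-sample subgroup) against 5.67, an unadjusted comparison that controls nothing.

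It would also be too strong to say that therapy is left largely uncontrolled. Therapy type is categorical, and analysis within therapy strata does control it, at a cost in precision.

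**Conclusion.** The concern holds in this limited form. The named confounding methods fit poorly with a continuous, time-varying exposure that has no defined groups. Matching would need an unstated cut-point and would drop unmatched patients, and neither method readily handles therapy that changes between visits together with other confounders.

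The size is not a document figure. Under the assumptions shown (30 to 35 pairs, SD 15, covariates explaining 20 to 30% of exposure variance), matched intervals are roughly 6 to 22% wider than those of an adjusted analysis of all 110. The loss from dichotomising comes on top and was the larger part in the simulation. The article's two stated precision figures are correct and need no change.

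**What to change.** Make the primary confounder adjustment a longitudinal mixed-effects regression with continuous, visit-specific activity. Adjust for age, baseline value of the outcome, tumour stage and subtype, and separate therapy indicators at each visit. Report each model with and without the visit-specific therapy terms: the Introduction links activity to better tolerance of treatment, so therapy received may partly mediate an activity effect. Examine effect modification through interaction terms. Keep matching only as a sensitivity analysis, with the cut-point, the number matched and the overlap reported. Present therapy contrasts as descriptive and say that limited overlap is possible.

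The cost is wording in the analysis plan. Section 3.3 reports recruitment as complete, and no new measurement is proposed. There are two downsides. The results rely more on model form, so linearity of the activity effect should be checked. The visit-specific indicators also need therapy dates, which are assumed to be in the clinical record; the article does not say so.

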**Discussion:**

Whereas most studies investigating the influence of physical activity in breast cancer patients focus on specific activities for three months or less, the BEGYN study will quantify the daily physical activity and cardiorespiratory fitness of breast cancer patients based on objective measurements in the context of the oncological therapy for 12 months after diagnosis. The study will reveal potential associations between exercise, immune status and physical as well as psycho-emotional outcome and the clinical course of the disease. Moreover, complementary therapies such as Vit D and Selenium supplementation and parameters investigating the motivation of the patients are part of the study. Due to this holistic approach, the BEGYN study will guide towards confirmatory studies on the role of physical activity in breast cancer patients to develop individualized counselling regarding the recommended type and extent of exercise.

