Studies that combine fitness tests, physical assessments, immunological markers, and psychological tests in breast cancer patients are still scarce, thus it is highly difficult to understand potential cross-links between these aspects. Filling this gap of knowledge could allow conclusions on individualized prevention and rehabilitation of the multiple sequelae that are potentially associated with breast cancer (9). Clinical studies in cancer patients must consider that according to current guidelines, all breast cancer patients are to be advised to exercise endurance and muscle strength (39). However, little is known on the extent to which patients adhere to this recommendation. Moreover, it would be unethical to withhold motivation for sportive activity from breast cancer patients for experimental purposes as a control. Thus, the BEGYN study was designed as an observational study, using validated methods to assess physical activity, cardiopulmonary fitness, body composition, psychological parameters, and extensive blood tests (e.g., immune status, vitamin D and selenium) during the first year of antineoplastic therapy after diagnosis of non-metastatic breast cancer. To gain information even after a longer period the BEGYN study is designed to collect data over one year after diagnosis. This study will shed light into the dynamics of physiological and psychological variables and the course of the disease during the first year after initiation of antineoplastic therapy in breast cancer patients in correlation with the physical activity. Ultimately, this study will lay the basis to develop individualized recommendations for exercise in breast cancer patients to improve the quality of life and prognosis.

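### Categorical confounders are handled by separate subgroup tests, with no step that combines the strata into one adjusted estimate and no interaction test

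*Protocol article*

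**What the plan says.** The confounding rule is one sentence in section 2.9: "Considering possible confounding we use subgroup analyses for categorical subgroups or propensity-score-matching otherwise". It has two branches. Categorical variables go to subgroup analysis, and propensity-score matching is kept for the remaining cases.

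The rest of the section lists the tests: t-tests, one-way and repeated-measures ANOVA, their rank-based counterparts, chi-squared and McNemar. It names no stratified estimator, covariate-adjusted model or interaction term. Significance is "two-sided p-values < 0.05", and "The statistical analyses are explorative, so there will be no correction for multiple testing".

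The sample size is justified only by the precision that all 110 patients give: a half-width of 2.835 for a mean, taking an SD of 15.0, and for a proportion "a width equal to 0.187 when the sample proportion is 0.50". No subgroup variable, subgroup size or target effect is stated.

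Two places in the Discussion bear on how subgroup results may be used. Section 3.1 hopes to find modifiers of patients' well-being. Section 3.1.3 says that patients on endocrine therapy, chemotherapy, surgery and radiotherapy can be compared.

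**The concern.** Stratification controls confounding only if the stratum results are then combined. If the combining step is left out, the analyst has several low-power results and no adjusted association. Matching does not repair this, because the sentence assigns it to the other branch.

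Separate tests also do not show whether the association of activity with an outcome differs between, say, patients with and without chemotherapy. That question needs the difference between the two associations, with its own standard error. A significant result in one part and a non-significant one in the other can easily arise when both parts share the same association. The between-group tests that section 2.9 does name compare outcomes between groups. They do not compare activity associations.

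At stake is the quality of the leads that the study passes on. A therapy-specific pattern produced by low subgroup power could misdirect the later studies, and a real common association could be reported as inconsistent.

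**Working it through.** **Inputs from section 2.9.** N = 110, SD 15.0, two-sided alpha 0.05, no multiplicity correction.

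**The plan's own figures.** The half-width for a mean is t(0.975; 109) × 15/√110 = 1.982 × 1.430 = 2.835. The width for a proportion is 2 × 1.96 × √(0.25/110) = 0.187. Both reproduce, and both describe the whole cohort.

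**Assumptions, because the article gives no values.** Two subgroups totalling 110 (55/55, 70/40 or 80/30); the same true correlation r between activity and outcome in both; r from 0.10 to 0.50.

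**Formulas (Fisher z).**
- Subgroup signal: z_i = atanh(r) × √(n_i − 3)
- Power: p_i = Φ(z_i − 1.96) + Φ(−z_i − 1.96)
- Exactly one subgroup significant: p1(1 − p2) + p2(1 − p1)
- Pooled strata: z = atanh(r) × √(n1 + n2 − 6)
- 95% half-width of the difference: 1.96 × √(1/(n1 − 3) + 1/(n2 − 3))

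**At r = 0.30** (atanh = 0.3095):
- 55/55: z = 0.3095 × √52 = 2.232 and power 0.607 in each. Exactly one significant: 2 × 0.607 × 0.393 = 0.477.
- 70/40: powers 0.717 and 0.469. Exactly one: 0.717 × 0.531 + 0.469 × 0.283 = 0.513.
- 80/30: powers 0.775 and 0.363. Exactly one: 0.775 × 0.637 + 0.363 × 0.225 = 0.576.
- Pooled: z = 0.3095 × √104 = 3.156, power 0.884.

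**Chance that exactly one subgroup is significant, by assumed r:**

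| r | 55/55 | 70/40 | 80/30 |
|---|---|---|---|
| 0.10 | 19.9% | 19.9% | 20.1% |
| 0.20 | 42.7% | 43.7% | 45.5% |
| 0.30 | 47.7% | 51.3% | 57.6% |
| 0.40 | 23.6% | 29.9% | 41.2% |
| 0.50 | 4.4% | 8.8% | 18.7% |

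**Precision of the difference (Fisher z scale).** The half-width is 0.38 (55/55), 0.40 (70/40) or 0.44 (80/30). For scale, r = 0.40 in one subgroup against r = 0 in the other is a difference of atanh(0.40) = 0.42.

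**Cross-check with the test that section 2.9 names.** Take a t-test of active against inactive patients (assumed 1:1) and a common effect with 80% power in all 110 (d = 0.54, or 0.54 × 15 = 8.1 points). In two equal subgroups the power is 0.50 each, so exactly one is significant in 2 × 0.50 × 0.50 = 50% of studies. In a simulation of the same setting, an interaction test declared a difference in 5% of runs, and the pooled estimate kept about 80% power. With three or four equal subgroups, some but not all are significant in 69% and 72%. With no effect at all, the two-subgroup figure is 2 × 0.05 × 0.95 = 9.5%.

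**The case against.** The strongest reply is that this is an explorative study described in a condensed article, and that an analysis plan that is not shown may say how strata are combined and may add interaction terms. If the article were merely silent, that would settle the matter. But the sentence names a method for a declared purpose, and the method as named does not serve it. A fuller plan that followed the sentence would inherit the problem.

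The explorative label does count. It justifies the absence of multiplicity correction and limits how far any result may be taken. It does not turn split testing into adjustment.

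Three further objections stand, and they narrow the point:
- A reader might infer that individualised exercise advice is to be taken from the subgroups. The text does not support this. Section 2.9 uses subgroups for confounding only. The Introduction says "this study will lay the basis to develop individualized recommendations for exercise in breast cancer patients". The Abstract's Discussion does look to "develop individualized counselling regarding the recommended type and extent of exercise", but puts confirmatory studies first.
- A reader might infer that the overall association is tested on half the data. Nothing says that subgroup analyses replace whole-cohort ones, and the precision figures use all 110.
- Propensity-score matching would normally give one adjusted comparison, so it would be wrong to say that section 2.9 has no adjusted estimate at all. The gap is in the categorical branch.

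It is also fair that the article nowhere says a significant and a non-significant subgroup will be read as different. The point is that its named methods offer no other way to judge a difference in association.

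**Conclusion.** The point holds for categorical confounders. The rule in section 2.9, followed as written, gives neither an adjusted association nor a valid comparison of associations between subgroups. It should be changed. It does not undermine the study, which already presents its analyses as explorative.

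The size is conditional. For a moderate common correlation of 0.20 to 0.30, two subgroups disagree on significance in roughly 43 to 58% of studies. The figure falls to about 20% at r = 0.10, 24 to 41% at r = 0.40 and 4 to 19% at r = 0.50. A reader might take about one half as a general rate. It is not one, because it applies to moderate effects and two subgroups. The loss from not pooling is clearest at r = 0.30, where subgroup power is 36 to 78% against 88% pooled. All these figures rest on assumed correlations and splits; the article gives neither.

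**What to change.** Replace the confounding sentence in section 2.9 with wording such as:

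> For categorical confounders, the association is estimated in one model on the whole cohort, stratified by or adjusted for the confounder (e.g. therapy type). Propensity-score matching may be used as a sensitivity analysis. A difference between subgroups is reported only as the activity-by-subgroup interaction with its 95% confidence interval. Significance in one subgroup and not in another is not read as a difference.

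The aims need no change, since the document already calls the analyses explorative.

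The cost is wording and one interaction term per subgroup question, with no extra patients, visits or measurements. Section 3.3 reports recruitment as finished, which does not prevent a change to the analysis. The downside is that interaction intervals will be wide (half-width about 0.38 to 0.44 on the Fisher z scale), so some subgroup statements will have to be dropped.
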